### Figure 7. Assumptions of the MRC Guidance on Process Evaluation

[39, 64]

[figure not shown]

This qualitative research will:

- Inform the refinement of the intervention (e.g. CFHealthHub, training of interventionists, initial assessments, manualised instructions) and its implementation (e.g. introduction within a CF Unit) for use in the full trial.
- Inform refinement to trial procedures for the full trial.
- Inform the selection of the final secondary measures used in the full trial to ensure they address the perceived benefits of the intervention.
- Help to understand the extent of any leakage of the intervention to controls.

### 11.3 Combining data and findings from the different components

We will use Farmer's triangulation protocol to display the findings from each component of the study together and discuss as a team the extent to which findings converge, complement each other or contradict each other [65, 66]. For example, we will display all findings about recruitment together to consider the feasibility of recruitment for the full trial and the actions required to ensure feasibility. We will also display in a matrix the qualitative and quantitative data for individual PWCF who have received the intervention and been interviewed [66]. We will use this to consider the extent to which our secondary outcome measures identify issues raised by PWCF in the interviews.

## 12. Monitoring

### 12.1 Oversight

The CTRU SOP GOV003 Data Monitoring and Ethics Committee states "A DMEC does not need convening in studies that carry low risk to patients". This project involves

delivering a behaviour change intervention through the website CFHealthHub and would therefore be classified as low risk.

The overall responsibility for the study will be with Sheffield Teaching Hospitals NHS Trust who will act as sponsors for the study. The local Principal Investigator (PI) will be responsible for the study at each participating site and it will be registered and approved with each local R&D department. The study will be conducted in accordance with the protocol, GCP and Sheffield CTRU Standard Operating Procedures. The two committees which will govern the conduct of the study are:

1. Programme Steering Committee (PSC)
2. Project Management Group (PMG)

The PSC will be responsible for the overall conduct of the trial and consists of an independent chair and four other independent members including a statistician and PPI representative. The committee will meet every 6 months to monitor the study.

The PMG will comprise of the trial manager and the core research team. The PMG will meet on a monthly basis to monitor the day-to-day running of the trial. The Trial Manager will be jointly supervised by the CI and the Assistant Director of CTRU via the form of regular meetings (face to face and telephone calls). The Trial Manager will be responsible for liaising with the whole project team. Trial monitoring procedures will be assessed based on the level of risk of the study. The Site Monitoring Plan will outline the types and frequency of site monitoring activities for the study and this will be agreed with the Sponsor prior to the start of the study.

## 12.2 Description of any interim analyses and stopping guidelines

There are no planned interim analyses or stopping guidelines for this study.

## 12.3 Harms (safety assessments)

### 12.3.1 Serious Adverse Events

Trial sites are to report Serious Adverse Events (SAEs) in conjunction with the CTRU standard operating procedure PM004 (Adverse events and serious adverse events). The definition of an SAE is as follows:

- results in death;
- is life-threatening\* (subject at immediate risk of death);
- requires in-patient hospitalisation or prolongation of existing hospitalisation;\*\*
- results in persistent or significant disability or incapacity;
- consists of a congenital anomaly or birth defect; or,
- is another important medical event that may jeopardise the subject.\*\*\*

\* 'life-threatening' refers to an event in which the patient was at risk of death at the time of the event; it does not refer to an event which hypothetically might have caused death if it were more severe.

\*\*Hospitalisation is defined as an inpatient admission, regardless of length of stay, even if the hospitalisation is a precautionary measure for continued observation. Hospitalisations

for a pre-existing condition, including elective procedures that have not worsened, do not constitute an SAE.

\*\*\*Other important medical events that may not result in death, be life-threatening, or require hospitalisation may be considered a serious adverse event/experience when, based upon appropriate medical judgment, they may jeopardise the subject and may require medical or surgical intervention to prevent one of the outcomes listed in this definition.

It is not anticipated that there will be many SAEs related to the behaviour change intervention. We will report any SAEs which are deemed related to the trial intervention and unexpected to the Sponsor within the specified timeframes below (12.3.4).

### **12.3.2 Adverse events we require reporting:**

We do require that sites report any new diagnosis of depression which requires treatment with medication or psychological therapy e.g. Cognitive Behavioural Therapy (CBT).

### **12.3.3 Expected SAEs and adverse events**

Certain adverse events are common to CF and associated medications. Expected SAEs must be reported in the annual safety report. Hospitalisation as a result of an exacerbation will be recorded in the study database and not be reported as an SAE.

Expected AEs in relation to medications or common in patients with CF

1. Acute FEV1 drop >15% after 1st dose of medication
2. Increased productive cough
3. Nasal congestion or stuffy nose
4. Chest congestion
5. Wheezing
6. Chest pain or chest discomfort
7. Voice alteration/change
8. Dyspnea (breathlessness)
9. Haemoptysis (coughing blood)
10. Rhinitis
- 11.
12. Headache
13. Crackles in lung
14. Throat irritation/ sore throat

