## 6.5 Usual care

Patients in both arms will receive usual care. Usual care is heterogeneous within and between centres, based on the needs of patients and the skills and interests of CF Unit staff. To better understand the configuration of usual care at participating centres a survey tool will be administered by the CTRU to the lead clinician at the centre. This will identify the spectrum of clinical and behaviour change interventions that are in use in the management and self-management of CF.

A minor component of the intervention is to train all members of the MDT in awareness of patient activation so that they are open to addressing issues raised for PWCF in the intervention arm. In addition, a staff member in the MDT will help to deliver the intervention. There is the possibility that the awareness of patient activation will have some effect on PWCF in both the intervention and control arms, and of leakage of the learning from the behaviour change component of the intervention to controls. We will investigate this possibility during the process evaluation.

Members of the MDT at each centre will receive one half-day, on-site, face-to-face training about the importance of objective nebuliser adherence data in the management of CF, and awareness of the importance of building patients' knowledge, skills and confidence to enable them to self-manage their treatment. This will include training in the interpretation of graphs and charts of objective adherence data produced by CFHealthHub, and the rationale for reducing target adherence in poor adherers in order to increase confidence. This will be delivered by designated members of the ACtiF research team.

Participants in the control arm will use a microchipped nebulizer but will not be able to access adherence data or other content and tools through CFHealthHub, neither will they receive the structured CFHealthHub intervention as described in the intervention manual. Control arm participants using Bi-neb nebulizers might have access to their data as part of routine care but this will not be in the user friendly format provided by the intervention.

One function of the qualitative research interviews with staff and control participants (see Section 8 below) is to understand the extent to which the patient activation awareness training has affected staff behaviour and whether control arm participants have received some aspects of the behaviour change intervention.

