#### **7.4.1 Primary clinical outcome**

The primary clinical outcome is the number of pulmonary exacerbations in 5 (+/-1) month post-baseline follow-up period, defined according to the Fuchs criteria [47]. An exacerbation of respiratory symptoms will be said to have occurred when a patient was treated with parenteral antibiotics for **any one of the following 12 signs or symptoms** [48]:

1. change in sputum;
2. new or increased hemoptysis;
3. increased cough;
4. increased dyspnea;
5. malaise, fatigue, or lethargy;

6. temperature above 38 °C;
7. anorexia or weight loss;
8. sinus pain or tenderness;
9. change in sinus discharge.
10. change in physical examination of the chest, derived from notes by site staff.
11. decrease in pulmonary function by 10 percent or more from a previously recorded value, derived from notes by site staff; or,
12. radiographic changes indicative of pulmonary infection, derived from notes by site staff.

The trial interventionist or prescribing clinician/nurse will collect data on the “exacerbations” form at the point of a participant starting a course of IV antibiotics.

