Further analyses with the objective nebuliser data will be performed to explore the process of habit formation with the delivery of the adherence intervention. The analyses will include:

- (a) generating objective habit scores by taking into account time of nebuliser use
- (b) using statistical process control to identify when periods of stability is achieved
- (c) other time-series methods, including cross-correlation between habit scores and adherence.

Adverse events will be based on serious adverse events (SAE) case report forms. A serious adverse event is defined as any adverse event or adverse reaction that results in death, is life-threatening, requires hospitalisation or prolongation of existing hospitalisation, results in persistent or significant disability or incapacity, or is a congenital anomaly or birth defect.

The following summaries will be presented as overall rates and stratified by AE classification:

- the number and percentages of patients reported as having Serious Adverse Events (SAE) in each treatment arm; and,
- the number and percentages recorded as having all forms of Adverse Events (AE) in each arm.

This information along with the acceptability of the study design and protocol to patients/GPs; the safety of the intervention; patient recruitment and attrition/retention rates will enable us to determine whether or not the definitive RCT is feasible within a satisfactory timescale and cost envelope using UK centres alone.

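### The SAE definition in 11.1 counts exacerbation admissions that 12.3.3 keeps off the SAE forms, so the by-arm SAE percentages will not match their own definition

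*Protocol*

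**What the plan says.** Four parts of the protocol bear on which admissions count as SAEs.

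- **Section 11.1 (analysis).** An SAE is an adverse event or reaction that is fatal, is life-threatening, "requires hospitalisation or prolongation of existing hospitalisation, results in persistent or significant disability or incapacity, or is a congenital anomaly or birth defect". There is no exacerbation exemption and no cross-reference to section 12.3. The source is fixed: "Adverse events will be based on serious adverse events (SAE) case report forms". The number and percentage of participants with reported SAEs are then given for each arm.
- **Section 12.3.1 (site definition).** It also includes inpatient hospitalisation, and adds a limb missing from 11.1: an event that "is another important medical event that may jeopardise the subject". Some admissions for pre-existing conditions are excluded.
- **Section 12.3.3 (expected events).** "Hospitalisation as a result of an exacerbation will be recorded in the study database and not be reported as an SAE". No form is named, and nothing is said about an admission judged related to the intervention.
- **Section 12.3.4 (reporting).** All adverse events, serious or not, go on the case report form. SAEs judged related go to the trials unit within 24 hours.

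On recording, section 7.4.1 has the exacerbations form completed "at the point of a participant starting a course of IV antibiotics". Table 3 lists its content as parenteral antibiotics plus the 12 signs and symptoms. Inpatient IV days and unscheduled inpatient stays are on the resource use form (section 7.4.2, item 14), which Table 3 marks at 5 months only. Sections 6.4.4.6 and Table 3 continue exacerbation collection to 30 April 2017.

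**The concern.** A table whose heading, definition and source forms disagree cannot be read at face value. Someone using 11.1 alone would take the SAE percentages to include admissions for exacerbation, the most obvious serious event in this population and the one the intervention is meant to reduce. Under 12.3.3 those admissions never reach the SAE forms.

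Section 11.1 also says that the safety of the intervention will inform whether the definitive trial is feasible. There is no data monitoring committee (12.1) and no interim analysis (12.2), so this by-arm table is one of the main safety outputs. The relatedness route is affected too: the expedited path in 12.3.4 starts from an SAE judged related, and on a literal reading an exacerbation admission never enters it.

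**Working it through.** The protocol has no figure to reproduce here. The check is mainly a comparison of the sections.

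**Does the table match its definition?**

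| Event | 11.1 definition | 12.3.1 | 12.3.3 | In a table built from SAE forms? |
|---|---|---|---|---|
| Admission for an IV-treated exacerbation, no other serious feature | SAE | SAE | not reported as SAE | No |
| Same, judged related to the intervention | SAE | SAE | no proviso | No, read literally |
| Fatal or life-threatening exacerbation | SAE | SAE | only the hospitalisation is exempt | Yes |
| Important medical event, no admission or other limb met | not an SAE | SAE | not addressed | Yes, if the site reports it |

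The first two rows are events that the analysis definition counts and the table omits. The last row is the reverse: the table may hold events outside its definition. The pre-existing-condition exclusion in 12.3.1 does not settle the first row, because an exacerbation is a worsening of the condition.

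**Where is an exempt admission recorded, and until when?** The described route is the resource use form at 5 months. Appendix 1 anticipates first enrolment on 2 May 2016, recruitment lasts four months, and the final research visit falls 4 to 6 months after consent.

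- Earliest final visit: 2 May 2016 + 4 months = 2 September 2016, just under 8 months before 30 April 2017.
- Latest final visit: about 2 September 2016 + 6 months = 2 March 2017, just under 2 months before 30 April 2017.

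So for about 2 to 8 months per participant, exacerbations are still collected but no described item shows whether the participant was admitted.

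**How many admissions might this be?** The documents give no admission rate, so this is an illustration only.

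- Section 2.1 reports 171,907 IV antibiotic days in the UK in 2012, of which 93,455 were in hospital: 93,455 / 171,907 = 54.4%.
- Over about 10,000 people: 93,455 / 10,000 = 9.35 inpatient IV days per person-year.
- Low case, 24 per arm (half of 48) for 4 months: 9.35 × 4/12 × 24 ≈ 75 days. High case, 32 per arm (half of 64) for 6 months: 9.35 × 6/12 × 32 ≈ 150 days.
- Assumed stay of 10 to 21 days (not in the documents): 75 / 21 ≈ 3.6 and 150 / 10 ≈ 15.

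That is roughly 4 to 15 admissions per arm. It assumes that trial participants match the national average, which includes children, and that all inpatient IV days are for exacerbations. These are admissions, not participants, so the effect on the percentages would be smaller if some people are admitted more than once.

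**The case against.** The best defence is that the exemption is deliberate and legitimate. Endpoint events are often kept out of SAE reporting. Table 3 is consistent with this: exacerbations have their own row and the safety row is labelled as other SAEs. Section 11.1 tabulates patients reported as having SAEs, and 12.3.4 refers back to the definitions before it, so both can be read with 12.3.3 in mind. That answers any charge that the exemption itself is an error. It does not make 11.1 carry the exemption, and it supplies neither a companion row nor a proviso for related events.

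Several stronger readings are tempting, but the documents do not support them.

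- *Harm would go unseen.* IV-treated exacerbations are the primary clinical outcome, and 11.1 compares them by arm with a 95% confidence interval.
- *Exempt admissions are recorded nowhere.* Section 12.3.3 says that they go in the database. Table 3 introduces the exacerbations form content as a non-exhaustive list, and the form is not shown. An item missing from that list may still be on the form.
- *Deaths and life-threatening exacerbations escape.* Only the hospitalisation is exempt; the other limbs of 12.3.1 still apply.
- *Admissions without IV antibiotics fall through.* They are not exacerbations under 7.4.1, so the exemption does not reach them.
- *No relatedness assessment takes place.* Section 12.3.4 has the local principal investigator assess adverse events. What is missing is a statement of what follows if an exempt admission is judged related.
- *Every hospitalisation counts under 11.1.* It covers only those required by an adverse event or reaction.
- *The protocol names a route to harm.* Section 6.5 mentions staff training in "the rationale for reducing target adherence in poor adherers in order to increase confidence". It describes no harm from this, and says that the training may affect both arms.

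**Conclusion.** The concern holds as an inconsistency with a limited effect. As written, the by-arm SAE percentages leave out exacerbation admissions that the 11.1 definition includes, and 11.1 drops one limb of the site definition. Exacerbation admissions have no stated by-arm summary of their own, and the exemption is silent on related events. The described record of inpatient stays stops about 2 to 8 months before exacerbation collection does, on the anticipated dates.

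The omission conclusion rests on the text alone. The 4 to 15 admissions per arm rests on national averages and an assumed length of stay, and serves only to show that the number is unlikely to be trivial. The recording gap depends on an exacerbations form that is not shown. The trial's feasibility criteria and its primary clinical comparison are unaffected. This should be corrected because it changes what a main safety table means, at very little cost.

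**What to change.** 1. Reconcile 11.1, 12.3.1, 12.3.3 and 12.3.4. Use the 12.3.1 definition in 11.1 and label the table as SAEs excluding exacerbation hospitalisations.
2. State in 12.3.3 that the exemption does not cover an admission judged related to the intervention or one meeting another seriousness limb.
3. Name the form on which exempt admissions are recorded. Make sure that it captures admission (yes/no) and relatedness as assessed by the principal investigator, through 30 April 2017, if the case report form does not already do so.
4. Report exacerbation admissions by arm in a separate row beside the SAE table. State the observation window of that row, because Table 3 schedules the other SAEs only at clinic visits and 5 months.

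The cost is protocol wording, at most two items on an existing form, and one table row. The downside is a short principal investigator assessment for each exacerbation.

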15. URTI
16. Sinusitis
17. Deafness
  
18. Indigestion / reflux
19. Tonsillitis
20. Joint pain
21. Decreased appetite
22. Fatigue
23. Headache

24. Distal intestinal obstructive syndrome
25. Fever
26. Otitis media or ear infection
27. Conjunctivitis
28. Pneumothorax
29. Decreased exercise tolerance
30. Pyrexia
31. Abdominal pain
32. Influenza
33. Pseudomonas infection
34. Vomiting
35. Diabetes
36. Pneumonia

### 12.3.4 Reporting

Adverse events and SAEs can be reported for participants at any stage of their trial participation. A member of the site study team (interventionist, clinician or other) will enquire about any adverse events at routine clinic appointments. These will be recorded on the adverse event section of the paper CRF and database. The event will be assessed by the local Principal Investigator and the form will be kept in the site file. Serious adverse events will be reported in the periodic safety reports to the research ethics committee and Trial Steering committee.

All adverse events (serious or other based on the definitions above) will be recorded on the case report form and details will be **entered on the study database within 1 week of completing the paper form**. Any SAEs which are deemed related to the trial intervention, the site will complete the paper CRF and **fax details this form to the CTRU within 24 hours of becoming aware of the event** in order for the CTRU to report this event to the Sponsor and the main REC within the required timeframes (15 days).

In participants using the Bi-Neb, any Adverse or SAEs relating to the use of Promixin via this device will be reported to the Patient Support team (PSP) at Phillips as per their standard practice.

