### 6.4.4 Procedures

The BCI will be delivered over a 4 to 6 month period through a combination of face-to-face sessions and contact via telephone with an interventionist, and through participant interaction with different modules of content available on CFHealthHub. The interventionist will discuss participant data with members of the MDT to ensure that care is informed by objective adherence data. If any concerns become apparent as the interventionists collect data and work with participants, these concerns will be passed onto the clinical team. The clinical team will

follow their standard procedures in relation to any concerns raised. The intervention content and delivery flow are outlined in Figure 5 and described below:

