Participating centres will provide participants with contact details, typically telephone numbers, but other methods may be volunteered by centres. Contact details will be provided so that participants can contact the centre if they have queries or problems regarding CFHealthHub between visits. The interventionist will be able to feedback any information from the intervention delivery **after** the baseline intervention visit to members of the wider CF team. This may include adherence data from sessions with the participant's clinician and MDT particularly if the participant raises any concerns or issues e.g. side effects of a drug to allow their usual clinician to discuss this with them at their next clinic visit.

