#### *6.4.4.5 Subsequent Review (intervention arm)*

Following these two sessions the amount of interaction which each PWCF has with the interventionist will be tailored to their needs and requirements although it is anticipated that these will normally marry with routine clinic visits: They may have additional face-to-face sessions or contact via telephone or e-mail. No more than one monthly face-to-face session will be conducted because of the research protocol; if the participant requests additional support, the centre may accommodate this at their discretion. Review meetings will take 30 minutes and be conducted over the 5month (+/- 1 month) of the follow-up period. The structure of review sessions will follow the same pattern as for 6.4.4.4.

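### Extra interventionist contact can modestly inflate the intervention arm's adverse-event percentages, and the protocol asks for no record of where each event was found

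*Protocol*

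**What the plan says.** On finding and recording events, protocol section 12.3.4 says two things. Active enquiry is at clinic: "A member of the site study team (interventionist, clinician or other) will enquire about any adverse events at routine clinic appointments". Recording is not limited to those visits: "Adverse events and SAEs can be reported for participants at any stage of their trial participation".

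On contact, the arms differ by design. The intervention arm has the initial intervention visit (6.4.4.2), the review visit (6.4.4.4) and then follow-up tailored to need (6.4.4.5): "They may have additional face-to-face sessions or contact via telephone or e-mail". Protocol-driven face-to-face review is capped: "No more than one monthly face-to-face session will be conducted because of the research protocol". Controls do not have these sessions. Under section 6.5 they cannot see their data through CFHealthHub, "neither will they receive the structured CFHealthHub intervention as described in the intervention manual".

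On what happens to information from those sessions, section 6.4.4 says: "If any concerns become apparent as the interventionists collect data and work with participants, these concerns will be passed onto the clinical team". Section 6.4.4.4 allows feedback to the wider team, "particularly if the participant raises any concerns or issues e.g. side effects of a drug".

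On analysis, section 11.1 will present patients with serious AEs per arm and "the number and percentages recorded as having all forms of Adverse Events (AE) in each arm". It lists the safety of the intervention among the items that inform whether the definitive trial is feasible. Section 12.3.2 singles out new depression needing treatment as an AE that sites must report. Section 9.4 blinds only the statisticians.

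**The concern.** A by-arm AE percentage measures the intervention's effect on AEs only if an event of a given kind has the same chance of being recorded in either arm. Here the intervention arm has additional conversations about treatment, beliefs, barriers and confidence. They are held by unblinded staff who may also be the ones asking about AEs, and there is an explicit route from those conversations to the clinicians. An event mentioned there may be recorded when the same event in a control participant would not be.

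The likely direction is towards more recorded AEs in the intervention arm. That could look like harm, or could offset a real reduction. The point goes beyond tabulation detail that could wait for the analysis plan: if the contact at which an event came to light is not collected, no later analysis can separate closer observation from a true difference.

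**Working it through.** The protocol gives no AE rate, detection rate or number of clinic visits, so there is no plan figure to reproduce. The size can only be illustrated.

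**Inputs from the protocol.** Target 64 participants, allocated equally, so about 32 per arm (sections 8.1.2 and 9.1). Two sessions are specific to the intervention arm before tailoring begins (6.4.4.5 refers back to two sessions).

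**Assumptions.** The same true AE risk in both arms, 50%, so 16 of 32 patients have an event. There are *c* = 2 or 3 common contacts, *k* = 2 extra contacts in the intervention arm, and each contact detects an event with probability *d*, independently.

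**Formula.** Share recorded: control 1 − (1 − d)^c; intervention 1 − (1 − d)^(c + k).

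| c | d | Control | Intervention | Ratio | Patients of 32, control v intervention |
|---|---|---|---|---|---|
| 2 | 0.3 | 0.51 | 0.76 | 1.49 | 8.2 v 12.2 |
| 2 | 0.5 | 0.75 | 0.94 | 1.25 | 12.0 v 15.0 |
| 2 | 0.7 | 0.91 | 0.99 | 1.09 | 14.6 v 15.9 |
| 3 | 0.3 | 0.66 | 0.83 | 1.27 | 10.5 v 13.3 |
| 3 | 0.5 | 0.88 | 0.97 | 1.11 | 14.0 v 15.5 |
| 3 | 0.7 | 0.97 | 1.00 | 1.03 | 15.6 v 16.0 |

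These figures lean high. The model treats an intervention session as being as good at finding AEs as a clinic enquiry, although no AE question is set for those sessions. It also lets every contact find every event, whenever the event occurs.

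**Second illustration, based on recall.** Onset is uniform over 5 months, with common contacts at 2.5 and 5 months. An event can be recorded only if a contact follows within 1.5 months, with probability 0.8.
- Controls: onsets in months 1 to 2.5 and 3.5 to 5 are covered, so (3/5) × 0.8 = 0.48.
- One extra session at 1 month also covers months 0 to 1, so (4/5) × 0.8 = 0.64. Ratio 0.64/0.48 = 1.33.
- If events are remembered for 2.5 months, controls record 0.80. The arm with the extra session records 0.2 × 0.96 + 0.8 × 0.80 = 0.832, a ratio of 1.04.
- With a 2.5-month window and certain detection, both arms record everything and the ratio is 1.00.

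**Treated depression.** With an assumed true risk of 10% (3.2 of 32) and two extra contacts, the first model gives 1.6 v 2.4 patients (c = 2, d = 0.3) or 2.8 v 3.1 (c = 3, d = 0.5). The difference is below one patient even before allowing for the clinical record that such a diagnosis leaves.

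**The case against.** The strongest reply is that the only active enquiry in the protocol is symmetric. It takes place at routine clinic appointments, and no passage tells interventionists to ask about AEs at intervention sessions. Section 6.4.4.4 has side effects passed on so that the usual clinician can take them up at the next clinic visit, which is the shared enquiry point. Section 6.4.4.5 expects later sessions normally to coincide with clinic visits, and section 6.7.2 says the same where possible. All of this stands and reduces the gap. It does not remove it: the first two sessions, and calls or e-mails, can fall outside clinic, and a clinician told of a problem beforehand is more likely to raise and record it.

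A reader might infer that controls go unobserved between clinic visits. The protocol does not support that. Section 10.1.1 describes monthly calls to participants from the trials unit, contact when data stop uploading, and troubleshooting that can include home visits, none of it limited to one arm. These contacts concern data and prescriptions, not AEs.

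A reader might also infer a large bias. The recall model gives 0.90 v 0.48, a ratio of 1.87, if intervention participants are seen every month in addition to clinic. The arithmetic is right, but the scenario treats a ceiling as a schedule and separates sessions from clinic visits, contrary to section 6.4.4.5. A ratio of 1.80 in the first model, with five extra sessions, has the same defect.

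Nor do the documents show that treated depression would be seriously distorted. It needs a diagnosis and treatment, and so leaves a clinical record, as serious AEs do. Concomitant medications and resource use are collected in both arms at 5 months, and PHQ-8 at consent and 5 months (Table 3).

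Finally, the AE form and the safety operating procedure are not shown, so it cannot be said that the source of detection goes unrecorded in practice, only that the protocol does not call for it.

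**Conclusion.** The point holds in a limited form. Recording at any stage, extra contact in one arm, a route from that contact to the clinicians, unblinded sites and by-arm percentages together allow modest inflation of recorded AEs in the intervention arm. The size is unknown. With only the two extra sessions, the first model gives ratios of 1.03 to 1.49 and the recall model 1.00 to 1.33, all on assumed detection and timing. The effect approaches nil if clinic enquiry catches nearly everything, and is probably small for serious AEs and treated depression.

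A reader might infer that the effect could decide whether the main trial goes ahead. The protocol does not support that reading. Section 11.1 plans a mainly descriptive analysis without formal testing, no stop-go criterion in section 7.1 concerns safety, and safety is one of several inputs to the feasibility judgement. The change is still worth making now, because it is cheap, the missing information cannot be recovered later, and the pilot exists to test procedures for the full trial.

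**What to change.** 1. Keep all AEs in the main by-arm safety table. Moving session-detected events out of it would hide genuine events.
2. Add a field to the AE form for the contact at which the event came to light (for example clinic visit, 5-month visit, trials-unit call, intervention session, other).
3. Ask the same standard AE question in both arms at common contacts: clinic visits, the 5-month visit and the monthly trials-unit call in section 10.1.1. First confirm that the call takes place in both arms. Section 10.1.1 does not limit it, but the footnote to Table 4 says the monthly prescription check is for changes in the control arm and potentially also the intervention arm.
4. Add a supplementary by-arm table limited to events found at common contacts, shown beside the change in PHQ-8 and GAD-7, which both arms complete at the same times.

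The cost is one form field, slightly longer calls and one extra table.
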